## G. Statistical Analysis

Data analysis will perform in September 2023. The Kolmogorov-Smirnov test is used to assess normality, independent sample t-test is used if normally distributed data, and Mann-Whitney U test is used otherwise for non-normally distributed data. Continuous variables with normal distribution are represented by mean and standard deviation (SD), and variables with non-normal distribution are represented by median and interquartile range (IQR). Categorical variables are expressed as frequencies and proportions and analyzed using chi-square tests or Fisher exact tests.

Primary outcome is compared between the two groups using chi-square test or Fisher exact test, with differences between groups expressed as relative risk (RR) and 95% confidence interval (CI). The linear mixed-effects model is used to compare the secondary outcomes, with baseline (T0) values as covariates, treatment, time, and the interaction of time and treatment as fixed effects, and the subject's random intercept as a random effect to account for differences in time. The treatment-by-time interaction term is tested first. If significant, between- and within-treatment differences are tested for each time

---

point, and analyses are adjusted for multiple comparisons using the Bonferroni test for differences in within-treatment anxiety scores from baseline (T0). Otherwise, the main effect of treatment was tested next, and no Bonferroni correction was made for assessing the treatment effect at each time point. The difference and 95% confidence interval (CI) between medians were calculated with Hodges-Lehmann estimator. The relative risk (RR) and 95% CI were used to describe the differences in dichotomous outcomes. Data are analyzed using SPSS 25.0 (IBM Corp, Armonk NY) and hypothesis tests are two-sided at a level of 0.05.

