## J. Outcome measures

The primary outcome is the incidence of perioperative anxiety in patients from the day of surgery to 3 days after surgery after two sessions of tDCS intervention. Perioperative anxiety was measured using the Hospital Anxiety and Depression Scale-Anxiety (HADS-A) (**Appendix 1**). A HADS-A score of 8 or more is considered to be a patient experiencing anxiety. On the day before surgery, the researcher assesses the patient for anxiety in the ward treatment room (T0), followed by a second assessment of anxiety (T1) after the first tDCS intervention. On the day of surgery, the researcher conducted separate assessments before (T2) and after (T3) administering the second tDCS stimulus. Anxiety scores were assessed at two hours after surgery (T4), on the

---

first day after surgery (T5), the second day after surgery (T6), the third day after surgery (T7), and the third month after surgery (T8).

Secondary outcomes included anxiety scores (T1-T8), the incidence of postoperative delirium (POD, assessed by the Confusion Assessment Method [CAM] or Confusion Assessment Method intensive care unit [CAM-ICU] **[Appendix 2]** on the day of surgery and three days after surgery [T4-T7]); pain scores (assessed by the Numeric Rating Scale [NRS] **[Appendix 3]** at T4-T7); frail scores (assessed by the Fatigue, Resistance, Ambulation, Illness and Loss of Weight Index [FRAIL] **[Appendix 4]** at T5-T8); and sleep quality score (assessed by the Pittsburgh Sleep Quality Index [PSQI] **[Appendix 5]** at T4-T8).

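### Secondary scores are tested with a mixed model, but the only estimate and interval named for a continuous difference is an unadjusted Hodges-Lehmann one

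*Protocol*

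**What the plan says.** Three instructions in Protocol section III.G bear on continuous data.

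- A general opening rule, which names no outcomes. It begins "The Kolmogorov-Smirnov test is used to assess normality", sends normal data to a t-test, and continues "Mann-Whitney U test is used otherwise for non-normally distributed data".
- A specific rule for the secondary outcomes: "The linear mixed-effects model is used to compare the secondary outcomes, with baseline (T0) values as covariates". The model has treatment, time and their interaction as fixed effects and a random intercept per subject. On the order of testing: "The treatment-by-time interaction term is tested first". Then come differences at each visit or, if the interaction is not significant, the treatment main effect.
- Directly after these model steps: "The difference and 95% confidence interval (CI) between medians were calculated with Hodges-Lehmann estimator". The next sentence deals with binary data: "The relative risk (RR) and 95% CI were used to describe the differences in dichotomous outcomes".

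Section III.J makes the primary outcome binary ("The primary outcome is the incidence of perioperative anxiety in patients from the day of surgery to 3 days after surgery"). Every score is secondary: HADS-A at T1-T8, NRS pain at T4-T7, FRAIL at T5-T8 and PSQI at T4-T8. A T0 assessment is listed for HADS-A only.

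**The concern.** A reported effect should carry an interval and a p-value from the same analysis. Here the named test is a model of means that uses T0 and all visits. The named estimate is a rank-based contrast at a single visit that uses neither. A reader could meet a visit that is significant by the model beside an interval that includes zero. The interval would also give up precision that the model has already gained.

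The schedule in III.J gives 8 + 4 + 4 + 5 = 21 combinations of score and visit at which this can happen. The loss of T0 precision concerns the 8 HADS-A visits. The mismatch between a model of means and a rank estimator concerns all 21.

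**Working it through.** **Whether the two sentences meet.** The Hodges-Lehmann sentence stands between the mixed-model steps and the sentence on dichotomous outcomes. The primary outcome is binary and has its own test and RR. The only continuous outcomes in III.J are the secondary scores. The natural reading is therefore that Hodges-Lehmann is their effect measure.

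**What the estimator is.** It is the median of all between-group pairwise differences, and its interval inverts the Mann-Whitney test. It equals the difference between group medians only under special conditions such as a pure shift. For {0,1,5,6,7} against {0,0,1,6,9}, the 13th of the 25 ordered differences is 0, so Hodges-Lehmann gives 0; the medians are 5 and 1, which differ by 4.

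**Loss of precision.** For a T0 correlation r, dropping a linear T0 adjustment widens the interval by 1/√(1 − r²):

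- r = 0.5: 1/√0.75 = 1.15
- r = 0.7: 1/√0.51 = 1.40

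Simulated mean widths (Hodges-Lehmann / adjusted) agree broadly: 2.009/1.670 = 1.20 at r = 0.5 and 1.995/1.386 = 1.44 at r = 0.7.

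**Disagreement on significance.** From the protocol: 98 per arm, two-sided 0.05. Assumed, because the protocol gives no score distribution: integer scores on 0-21, mean 7, SD 3.5, true difference 1.2 (1.2/3.5 = 0.34 SD), r = 0.3, 0.5 or 0.7; 2,000 runs each. ANCOVA on T0 at one visit stands in for the mixed-model contrast, and the Mann-Whitney test stands in for the Hodges-Lehmann interval.

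| r | Adjusted significant | Mann-Whitney significant | Disagree |
|---|---|---|---|
| 0.3 | 69.1% | 63.9% | 11.7% |
| 0.5 | 77.5% | 63.3% | 19.1% |
| 0.7 | 89.7% | 63.1% | 28.5% |

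A repeat with a 0.35 SD effect gave 10%, 18% and 29%. With no effect, both tests stayed near 5% and disagreed in about 4-6% of runs.

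Trials in which only Mann-Whitney is significant = (disagreement − gap in power)/2, from the unrounded percentages:

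- r = 0.3: (11.7 − 5.2)/2 = 3.3%
- r = 0.5: (19.05 − 14.15)/2 = 2.5%
- r = 0.7: (28.5 − 26.6)/2 = 1.0%

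Most disagreements are therefore cases in which the adjusted analysis is significant and the unadjusted one is not.

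**A caution on ties.** On integer scores the Hodges-Lehmann limits are themselves integers. If an interval that ends exactly at zero counts as including zero, disagreement in a similar simulation was 43%, 53% and 65% at the three correlations. That reflects coarse scores and a convention, so it is not used as the size of the problem.

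**Sample size.** The stated figures concern only the binary primary outcome. For 51.4% against 0.6 × 51.4% = 30.84%, the pooled formula gives 89 per group against the stated 88, and 88/0.9 = 97.8, rounded up to 98. Neither bears on this point.

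**The case against.** The strongest reply is that the protocol never says Hodges-Lehmann applies to the secondary scores. It is the usual companion of Mann-Whitney and of median with IQR, so the sentence may serve the general opening rule and cover only baseline or perioperative variables. The mixed model is assigned to the secondary outcomes specifically, and a specific rule normally overrides a general one. The statistical analysis plan, which is not at hand, may settle the matter.

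The first part stands: the link is an inference from sentence order and the outcome list. It does not remove the problem. If Hodges-Lehmann covers the scores, test and interval do not match. If it does not, the section names an effect measure for binary outcomes and for unspecified variables, but none for the scores it models. Since the protocol itself fixes both test and estimator, it should say how they fit.

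Four stronger readings might be inferred, and the documents do not support them.

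- *That estimate, interval and p-value all have different sources.* Estimate and interval share one source; only the p-value comes from elsewhere.
- *That the normality test will almost always divert the scores to Mann-Whitney.* The protocol does not say which form of Kolmogorov-Smirnov is meant. On HADS-A-like scores the uncorrected form rejected in about 5% of simulated trials, against 88-90% for the Lilliefors form.
- *That the two analyses conflict equally in both directions.* Mann-Whitney alone was significant in only about 1-3% of trials.
- *That calling the estimate a difference between medians distorts results.* The two differed in roughly 40% of runs, but by more than one point in under 1%. It is loose labelling.

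**Conclusion.** The point holds in a limited form. Section III.G tests the secondary scores with a mixed model, while the only estimate and interval it names for a continuous difference come from an unadjusted rank procedure. For HADS-A the two would disagree on significance in about 10-29% of trials, mostly because the unadjusted interval is less precise. These figures rest on an assumed T0 correlation of 0.3 to 0.7, an assumed effect of about 0.35 SD, and a single-visit ANCOVA in place of the full model.

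No size is claimed for NRS, FRAIL or PSQI. III.J lists no T0 value for them, so the argument from T0 precision does not reach them; the mismatch between a model of means and a rank estimator does. The primary analysis and the sample size are untouched. This should be corrected, but it does not threaten the main conclusion of the trial.

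**What to change.** In section III.G:

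1. State that the linear mixed model is the inferential analysis of the repeated scores. Report its between-group mean difference with the model's own 95% CI, per visit when the interaction is significant and overall when it is not.
2. Adjust for T0 for HADS-A. For NRS, FRAIL and PSQI, use the same model without the T0 term unless a baseline value was recorded.
3. Limit the Kolmogorov-Smirnov / t-test / Mann-Whitney rule to named variables outside the mixed model.
4. If Hodges-Lehmann is kept for the scores, describe it as an unadjusted location-shift estimate (the median of pairwise differences), pair it with Mann-Whitney, and present it as a sensitivity analysis.

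The cost is a few sentences of wording. No new data are needed and the sample size does not change. For HADS-A the required estimates come from the model already planned; the other three scores need the model refitted without T0, or confirmation that a baseline exists.

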## H. Intervention with tDCS

The apparatus (machine manufacturer: Jiangxi Huaheng Jingxing Medical Technology Co.; machine specification model: MBM-I) is used in this trial. The electrostimulation is delivered through two electrodes placed in saline-soaked sponges. The electrodes are fixed by a stretchy hat, with the anode over the left DLPFC.

On the day before and the day of surgery, patients in the active-tDCS group receive 2 mA tDCS with a 30-s ramp-up phase at the beginning and a 30-s ramp-down phase at the end for 20 min. While patients in the sham-tDCS group only receive a 30-s ramp-up phase at the beginning and a 30-s ramp-down phase at the end of each session without a constant current of 2 mA for 20 min.

## I. Anesthesia protocol

Standard monitoring procedures are initiated as soon as patients arrive in the operating room, including electrocardiography, invasive arterial blood pressure, pulse oximetry, and central venous catheterization.

The patients are administered general anesthesia with 0.5 µg/kg sufentanil, 0.3 mg/kg etomidate, and 1 mg/kg rocuronium, the tracheal

---

catheter is inserted after the bispectral index value decreased to less than 60, and the anesthesia machine is used for mechanical ventilation with the end-expiratory carbon dioxide partial pressure maintained between 35 and 45 mmHg. Patients undergo ultrasound-guided bilateral transversus abdominis plane block with 40 ml of 0.375% ropivacaine and are transferred to the PACU after surgery. Intravenous infusion of propofol at a rate of 4-6 mg/kg/h and remifentanyl at a rate of 0.1-0.3 µg/kg/min, along with continuous inhalation of 1% sevoflurane are used to maintain bispectral index values between 40 and 60 for the anesthesia maintenance. If required, vasoactive drugs are used to maintain hemodynamic stability during anesthesia.

Postoperative treatment: The tracheal catheter is removed after the patients regain consciousness from anesthesia, ensuring an optimal tidal volume. Postoperative analgesia is achieved with a patient-controlled intravenous infusion of 1.5 µg/kg sufentanil and 6 mg tropisetron with saline to 100 mL. The background infusion rate is 2 mL/h and the self-controlled analgesic dose is 0.5 mL.

## J. Outcome measures

The primary outcome is the incidence of perioperative anxiety in patients from the day of surgery to 3 days after surgery after two sessions of tDCS intervention. Perioperative anxiety was measured using the Hospital Anxiety and Depression Scale-Anxiety (HADS-A) (**Appendix 1**). A HADS-A score of 8 or more is considered to be a patient experiencing anxiety. On the day before surgery, the researcher assesses the patient for anxiety in the ward treatment room (T0), followed by a second assessment of anxiety (T1) after the first tDCS intervention. On the day of surgery, the researcher conducted separate assessments before (T2) and after (T3) administering the second tDCS stimulus. Anxiety scores were assessed at two hours after surgery (T4), on the

---

first day after surgery (T5), the second day after surgery (T6), the third day after surgery (T7), and the third month after surgery (T8).

Secondary outcomes included anxiety scores (T1-T8), the incidence of postoperative delirium (POD, assessed by the Confusion Assessment Method [CAM] or Confusion Assessment Method intensive care unit [CAM-ICU] **[Appendix 2]** on the day of surgery and three days after surgery [T4-T7]); pain scores (assessed by the Numeric Rating Scale [NRS] **[Appendix 3]** at T4-T7); frail scores (assessed by the Fatigue, Resistance, Ambulation, Illness and Loss of Weight Index [FRAIL] **[Appendix 4]** at T5-T8); and sleep quality score (assessed by the Pittsburgh Sleep Quality Index [PSQI] **[Appendix 5]** at T4-T8).

## K. Surgical Method

Laparoscopic colorectal tumor resection.

## IV. Adverse Events

An adverse event (AE) is an unforeseen medical event that occurs to a patient or a clinical study subject. The tDCS has been established as a safe and tolerable form of non-invasive brain stimulation. Adverse events commonly consist of paraesthesia, such as mild tingling, burning and itching, as well as headaches, and transient skin redness. In this trial, the investigator observes the patient's facial expression as the patients begin to receive the stimulation (avoided indicative questions such as asking if there is tingling, discomfort, etc.).

## V. DATE AND SAFETY MONITORING

Clinical research will formulate a corresponding data safety monitoring plan according to the size of the risk. In the implementation stage of clinical research, it will be to record all adverse events in detail, handle and track them

---

properly until they are properly resolved or the condition is stable, and report serious adverse events and unexpected events to the ethics committee, competent authorities and drug regulatory authorities in a timely manner as required. The principal investigator will periodically conduct a comprehensive review of all adverse events, and if necessary, an investigator meeting convened to assess the risks and benefits of the study. This experiment is a double-blind trial, and the blinding will be promptly unmasked if necessary to ensure the safety and rights of the subjects. We will arrange independent data monitors to monitor the research data, and high-risk studies will establish an independent data safety monitoring committee to monitor the accumulated safety data and efficacy data in order to determine whether to continue the study.

## **VI. FUNDING**

This study was supported in part by grants from the National Key R&D Program of China (2021ZD0203100 to J-LC; 2022ZD0206200 to SZ); National Natural Science Foundation of China (NSFC81720108013, NSFC31771161, and NSFC81230025 to J-LC; NSFC82171227 and NSFC81300957 to HL; NSFC81771453 and NSFC31970937 to HXZ; NSFC82371536 to SZ); Jiangsu Provincial Special Program of Medical Science (BL2014029 to J-LC); Basic and Clinical Research Center in Anesthesiology of Jiangsu Provincial "Science and Education for Health" Project (J-LC); Zhejiang Provincial Natural Science Foundation (LY22H090019 to HL); Jiangsu Provincial Natural Science Foundation (BK20190047 to HXZ); the Priority Academic Program Development of Jiangsu Higher Education Institutions (19KJA610005 to HXZ); Distinguished [name] of Jiangsu (HXZ); Jiangsu Province Innovative and Entrepreneurial Talent Program and Jiangsu Province Innovative and Entrepreneurial Team Program (HXZ); Xuzhou Medical University start-up grant for excellent scientist (D2018010 and D2019025D to HXZ); the Natural Science Foundation of Shanghai (21ZR1411300 to YH); and

---

Shenkang Clinical Study Foundation of Shanghai (SHDC2020CR4061 to YH).

## VII. INFORMATION CONFIDENTIALITY

Medical records will be kept in the hospital, and the investigators and ethics committees will be allowed to access the patient's medical records. Any public reporting of the results of this study will not disclose the patient's personal identity.

## Appendix 1. The Hospital Anxiety and Depression Scale

### The Hospital Anxiety and Depression Scale

Name :

Date:

Doctors are aware that emotions play an important part in most illnesses.  
If your doctor knows about these feelings he will be able to help you more.

This questionnaire is designed to help your doctor to know how you feel.  
Ignore the numbers printed on the left of the questionnaire. Read each item  
and underline the reply that comes closest to how you have been feeling in the  
past week.

Don't take too long over your replies: your immediate reaction to each item  
will probably be more accurate than a long thought-out response.

| questions                                                                                  | answers                                | score |
|--------------------------------------------------------------------------------------------|----------------------------------------|-------|
| 01. I feel tense or 'wound up' (A):                                                        | Most of the time                       | 3     |
|                                                                                            | A lot of the time                      | 2     |
|                                                                                            | From time to time, occasionally        | 1     |
|                                                                                            | Not at all                             | 0     |
| 02. I still enjoy the things I used
to enjoy (D):                                       | Definitely as much                     | 0     |
|                                                                                            | Not quite so much                      | 1     |
|                                                                                            | Only a little                          | 2     |
|                                                                                            | Hardly at all                          | 3     |
| 03. I get a sort of frightened
feeling as if something awful is
about to happen (A): | Very definitely and quite badly        | 3     |
|                                                                                            | Yes, but not too badly                 | 2     |
|                                                                                            | A little, but it doesn't worry me      | 1     |
|                                                                                            | Not at all                             | 0     |
| 04. I can laugh and see the funny
side of things (D):                                   | As much as I always could              | 0     |
|                                                                                            | Not quite so much now                  | 1     |
|                                                                                            | Definitely not so much now             | 2     |
|                                                                                            | Not at all                             | 3     |
| 05. Worrying thoughts go through
my mind (A):                                           | A great deal of the time               | 3     |
|                                                                                            | A lot of the time                      | 2     |
|                                                                                            | From time to time but not too
often | 1     |
|                                                                                            | Only occasionally                      | 0     |
| 06. I feel cheerful (D):                                                                   | Not at all                             | 3     |
|                                                                                            | Not often                              | 2     |
|                                                                                            | Sometimes                              | 1     |
|                                                                                            | Most of the time                       | 0     |

|                                                                               |                                       |   |
|-------------------------------------------------------------------------------|---------------------------------------|---|
| 07. I can sit at ease and feel relaxed (A):                                   | Definitely                            | 0 |
|                                                                               | Usually                               | 1 |
|                                                                               | Not often                             | 2 |
|                                                                               | Not at all                            | 3 |
| 08. I feel as if I am slowed down (D):                                        | Nearly all the time                   | 3 |
|                                                                               | Very often                            | 2 |
|                                                                               | Sometimes                             | 1 |
|                                                                               | Not at all                            | 0 |
| 09. I get a sort of frightened feeling like 'butterflies' in the stomach (A): | Not at all                            | 3 |
|                                                                               | Occasionally                          | 2 |
|                                                                               | Quite often                           | 1 |
|                                                                               | Very often                            | 0 |
| 10. I have lost interest in my appearance (D):                                | Definitely                            | 0 |
|                                                                               | I don't take so much care as I should | 1 |
|                                                                               | I may not take quite as much care     | 2 |
|                                                                               | I take just as much care as ever      | 3 |
| 11. I feel restless as if I have to be on the move (A):                       | Very much indeed                      | 3 |
|                                                                               | Quite a lot                           | 2 |
|                                                                               | Not very much                         | 1 |
|                                                                               | Not at all                            | 0 |
| 12. I look forward with enjoyment to things (D):                              | As much as ever I did                 | 3 |
|                                                                               | Rather less than I used to            | 2 |
|                                                                               | Definitely less than I used to        | 1 |
|                                                                               | Hardly at all                         | 0 |
| 13. I get sudden feelings of panic (A):                                       | Very often indeed                     | 0 |
|                                                                               | Quite often                           | 1 |
|                                                                               | Not very often                        | 2 |
|                                                                               | Not at all                            | 3 |
| 14. I can enjoy a good book or radio or TV programme (D):                     | Often                                 | 0 |
|                                                                               | Sometimes                             | 1 |
|                                                                               | Not often                             | 2 |
|                                                                               | Very seldom                           | 3 |

"(A)" scores were used to screen for the presence of anxiety symptoms;

A: \_\_\_\_\_

8~10: mild anxiety, 11~14: moderate anxiety, 15~21: severe anxiety

---

